### Secondary outcomes

Fasting blood glucose, serum C-peptide, blood lipid levels, glycogenesis serum protein, depression and anxiety will be measured in all PDPN participants. All the above measurements will be evaluated at baseline and in the 4th week.

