**Method and design:**

This will be a randomized controlled trial. A total of 150 participants will be recruited and assigned to one of three groups: the healthy group, the DM without PDPN group and the DM with PDPN group. Participants in the DM without PDPN and the DM with PDPN groups will each be further divided between an electroacupuncture group and a sham electroacupuncture group. Participants will receive six treatment sessions per week for 4 weeks. Multimodal cerebral imaging includes resting-state functional magnetic resonance imaging (rs-fMRI), diffusion tensor imaging (DTI) and magnetic resonance spectroscopy (MRS); this neurophysiological testing will be the primary outcome measure. Subjective pain scales and blood analysis will be a secondary outcome measure and will be used to assess the clinical efficacy of the intervention. Multimodal cerebral imaging will be used to detect cerebral activity changes in each treatment group. The clinical data and fMRI data will be analysed for all the groups. Multiple correlation regression analyses will be used to assess the association between changes in cerebral functional activity and the improvement of clinical outcomes after acupuncture treatment.

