## Recruitment criteria

### Inclusion criteria for participants with DM with PDPN

Meet the study’s clinical diagnostic criteria of PDPN;Aged 55–65 years (either sex), with a history of diabetes ≥ 5 years;Present with stable vital signs, with blood pressure, heart rate, blood lipids and other indicators within normal limits;Possess normal cognitive and expressive abilities and have no serious cardiovascular and cerebrovascular disease;Manifest no pre-existing peripheral nervous system lesions;Demonstrate a willingness to provide informed consent, participate voluntarily and cooperate with doctors to complete the clinical trial.

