### Sample size calculation

This proposed study is an RCT whose primary aim is to evaluate the cerebral imaging mechanism of acupuncture to improve cerebral central sensitization and the clinical effect of acupuncture in patients with PDPN. Acupuncture is a complex intervention that differs from other treatments. Its therapeutic effect is changed if the acupoints are altered. No two-arm, randomized, sham-controlled trial has been conducted on this topic. For this reason, we are using our previous clinical experience to calculate the efficacy of electroacupuncture as an intervention [30, 31]. The proposed sample size of this trial was calculated mainly based on the Short-Form McGill Pain Questionnaire and the assumption that after treatment, the average change reported using this questionnaire would be greater for the experimental group than for the control group. The mean difference was 0.81, with a standard deviation of 0.07. Sample size was calculated using a noninferiority comparison. We set the alpha risk (*α*, type 1 error risk) at 0.025, the beta risk (*β*, type 2 error risk) at 0.2 and the critical value (*Δ*) at − 0.1. Calculating by using SAS [32], the sample size result was 24. Thus, according to this sample size calculation, each group should recruit 24 participants. Allowing for a 20% attrition rate in this study, we plan to recruit 150 participants, with 30 in each of the study groups. Healthy participants will not receive any treatment. Each participant will receive 2 rs-fMRI scans to observe different cerebral activities before and after acupuncture treatment.

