
### Clinical data analysis

According to the study data, the effect indices of the two groups will be calculated and compared to analyse the influence on the prognosis of PDPN. Indices of scales will be analysed by repeating measurement analysis of variance. The main analytical indicators will be the curative effect index and recurrence rate. A *t* test will be used for measurement data with a normal distribution. The Wilcoxon rank sum test will be used for nonnormal distribution; the Pearson chi-square test will be used for counting data. If it is a sequential concatenation table, the CMHX^2^ test will be used.

The measurement data of different treatment groups will be statistically described by the mean ± standard deviation (‾*χ* ± s). Intragroup differences will be assessed using a t-test at baseline; analysis of variance (ANOVA) will be used to compare measurement data at different stages; and SNK will be used for pairwise comparisons. Changes between groups before and after treatment will be analysed by ANOVA. If the data do not fit the above statistical analysis conditions (such as nonnormal), a nonparametric test will be used.

Counting data from different treatment groups are statistically described by frequency (constituent ratio). Changes between groups before and after treatment will be tested using the X2 test (CMHX2 test) or nonparametric test. The analysis of data results from participants not complying with the study protocol will be treated according to statistical analysis with randomization and multiple interpolation.

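### Blood lipids are a secondary efficacy measure in PDPN participants admitted only with normal lipids, so a within-arm lipid change should not be read as a treatment effect

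*Protocol article*

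**What the plan says.** Four places in the protocol article bear on this point.

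- **Inclusion criteria for participants with DM with PDPN:** "Present with stable vital signs, with blood pressure, heart rate, blood lipids and other indicators within normal limits".
- **Secondary outcomes:** "Fasting blood glucose, serum C-peptide, blood lipid levels, glycogenesis serum protein, depression and anxiety will be measured in all PDPN participants". On timing: "All the above measurements will be evaluated at baseline and in the 4th week".
- **Abstract, Method and design:** "Subjective pain scales and blood analysis will be a secondary outcome measure and will be used to assess the clinical efficacy of the intervention".
- **Clinical data analysis:** two comparisons are planned for measurement data in general. Over time, "analysis of variance (ANOVA) will be used to compare measurement data at different stages". Between arms, "Changes between groups before and after treatment will be analysed by ANOVA".

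The article does not name the lipid fractions or the normal limits. It does not say whether the blood sample that establishes eligibility is also the baseline sample. The criteria for the diabetes-without-PDPN group list no lipid limit.

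**The concern.** One variable has two roles in the same people. It is an entry filter that requires normality, and it belongs to a group of measures meant to show clinical benefit. Lipids are the only blood outcome in the list that the PDPN criteria name as having to be normal (the criteria also mention other indicators, without defining them).

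Two consequences need to be kept apart.

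1. **Restricted range.** Participants with raised lipids are excluded, so there is no abnormality to correct, and improvement can only be movement within the normal range. This holds whichever sample is used as baseline.
2. **Regression to the mean.** If the reading that admits a participant is also the baseline, some participants qualify on a chance favourable value, and the retest moves back toward the population mean without any treatment effect. This holds only under that condition.

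At stake is how one secondary outcome is read. A within-arm rise could be reported as metabolic harm, or a flat result as absence of metabolic effect, when the entry rule alone could produce either.

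**Working it through.** The article gives no figure for this point, so there is none to reproduce. The check asks how large the before-after drift could be with no treatment effect.

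**Inputs from the article**
- Entry is limited to normal lipids, and measurement is at baseline and week 4 (sections cited above).
- Arm size: "with 30 in each of the study groups". With the stated 20% attrition, 30 × 0.8 = 24 are analysed per arm.

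**Assumptions, not in the article**
- The entry reading is the baseline reading.
- The lipid value is standardised and normal in otherwise eligible patients, and is cut off above at the normal limit. A fraction with a lower limit would mirror this, drifting toward its own abnormal side.
- The share f of otherwise eligible patients with normal lipids is 0.50 to 0.80.
- The four-week retest correlation r is 0.7 to 0.9.

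**Formulas.** Let c be the f-quantile of the standard normal and φ its density.
- Baseline mean after selection: −φ(c)/f
- Baseline variance after selection: v = 1 − c·φ(c)/f − (φ(c)/f)²
- Expected rise with no effect: (1 − r)·φ(c)/f
- Variance of change: (1 − r)²·v + 1 − r²
- Chance of a significant rise: upper tail of the noncentral t for a paired test at two-sided 0.05, n = 24

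**Worked ends of the range**
- f = 0.50, r = 0.7: φ(0)/0.50 = 0.399/0.50 = 0.80. Rise = 0.3 × 0.80 = 0.24 SD. SD of change = 0.74.
- f = 0.80, r = 0.9: c = 0.842 and φ(c)/0.80 = 0.280/0.80 = 0.35. Rise = 0.1 × 0.35 = 0.035 SD. SD of change = 0.44.

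| f | Baseline mean (SD) | Rise, r = 0.7 | Rise, r = 0.8 | Rise, r = 0.9 | False significant rise at n = 24, r = 0.7 / 0.8 / 0.9 |
|---|---|---|---|---|---|
| 0.50 | −0.80 | 0.24 | 0.16 | 0.08 | 33% / 23% / 13% |
| 0.67 | −0.54 | 0.16 | 0.11 | 0.05 | 17% / 13% / 8% |
| 0.80 | −0.35 | 0.10 | 0.07 | 0.035 | 10% / 8% / 6% |

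The nominal rate in that direction is 2.5%. At 30 per arm the range is 6% to 41%.

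**Between-arm contrast.** In a simulation of 20,000 trials with 30 per arm and no true effect (f = 0.5, r = 0.8), the within-arm rise was 0.161 SD and the paired test rejected in 29% of trials (two-sided). The difference in change between arms was 0.0 and rejected in 4.9%. Both arms pass the same filter, so the drift cancels.

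**Separate baseline sample.** When the baseline was a fresh reading taken after the eligibility reading, the within-arm change in the same simulation was −0.0009 SD, which is zero within simulation error.

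**Room to move.** Under the same model the baseline SD after selection is 0.60 of the unselected SD at f = 0.50 and 0.76 at f = 0.80. The range is narrowed, but it has not collapsed.

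**The case against.** The strongest reply is that the article plans the right comparison. It compares change between groups, and that randomised contrast is not affected by the entry rule. A drift common to both arms would also be visible in the sham arm. The across-stages comparison is worded for measurement data in general and does not name lipids. All of this stands.

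A reader might infer that the before-after change is biased toward worsening as a matter of fact. The article does not support that. The bias requires the eligibility reading to be the baseline, and no section says so. Which sample serves as baseline is operational detail that a condensed article can leave to the full protocol, so its absence here is not an error.

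A reader might also infer that the lipid outcome cannot show benefit at all. That does not follow either. The outcome is a continuous level, no normalisation or responder endpoint is defined, and values can fall within the normal range.

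It is also fair to say that the magnitude rests on assumed inputs and is small at the mild end (0.035 SD, 6% against 2.5%), that lipids are one item in a list of secondary measures, and that the efficacy label comes from a general sentence in the abstract.

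What remains is that the article admits only participants with normal lipids, lists lipids among measures of efficacy, and leaves a within-arm test open for them.

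**Conclusion.** The point holds in limited form and is minor. Entry on normal lipids leaves no abnormality to correct in the PDPN arms and reduces the room for improvement. A within-arm lipid change is therefore weak evidence of either benefit or harm. If the entry reading doubles as baseline, the within-arm change is also biased upward, by about 0.04 to 0.24 SD under the assumed shares and retest correlations. With a separate baseline sample the bias is about zero. The electroacupuncture-sham difference is unbiased in both cases. The sample size, the primary outcomes and the randomised contrast are not affected. The restricted range follows from the text alone. The size of the drift does not, because the share with normal lipids, the retest correlation and the use of the entry sample as baseline are all assumptions.

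**What to change.** For blood lipids in the PDPN arms:

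- Base any statement of treatment effect only on the week-4 electroacupuncture-sham difference adjusted for the baseline value.
- Present within-arm baseline and week-4 values descriptively, with no before-after test.
- State alongside the result that entry was restricted to participants with normal lipids.

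The outcome need not be deleted, and blood sampling, visits and sample size do not change. The cost is one line of wording and the loss of a within-arm test.

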#### Michigan Neuropathy Screening Instrument (MNSI)

The MNSI is simple, convenient and easy to perform, especially for doctors [23]. The MNSI is an effective screening test for diabetic neuropathy because of its accuracy [24]. The MNSI includes two parts: Part A evaluates a participant’s self-assessment of clinical symptoms using 15 “yes” or “no” questions, and part B measures participant symptoms according to a clinical evaluation. The MNSI will be used to assess participants at baseline and in the 4th week.

#### Neuropathic Pain Symptom Inventory (NPSI)

The NPSI is an instrument for evaluating the different symptoms of neuropathic pain [25]. The NPSI is suitable for use in clinical trials because of its good construct validity, its high test-retest reliability and its sensitivity to change. According to the overall impression assessment of participants and examiners on pain changes, the increase or decrease in the total NPSI score is related to improvement or changes in subjective pain. NPSI will be used to assess participants at baseline and in the 4th week.

#### Leeds Assessment of Neuropathic Symptoms and Signs (LANSS)

The LANSS can distinguish patients with neuropathic pain from those with nociceptive pain [26]. It is based mainly on the analysis of sensory descriptions and the inspection of sensory abnormalities. There are 7 questions on the LANSS, and the sensory descriptions include abnormal pain sensation, autonomic nerve dysfunction, tactile pain, paroxysmal pain and skin temperature changes. The evaluation of paraesthesia will include hyperalgesia and acupuncture threshold changes. This method of setting items may increase the discriminative ability of each item. The LANSS will be administered at baseline and in the 4th week.

#### Brief Pain Inventory (BPI)

The BPI is a self-administered questionnaire used to assess pain severity and the effect of pain on the daily function of patients. BPI produces pain severity and pain interference scores ranging from 0 to 10; higher scores indicate worse pain [27, 28]. The BPI has a short and a long form. There are 15 questions on the Short Form BPI (9 questions, with the last question containing 7 parts). In PROMIS calibration testing, 11 of the 15 questions were administered (BPI Items 1, 2, 7 and 8 were omitted). The BPI will be assessed at baseline, the 1st, 2nd, 3rd and 4th weeks of the treatment period, and at the 1-, 2-, 3- and 6-month follow-ups after treatment.

#### Short-Form McGill Pain Questionnaire

The Short-Form McGill Pain Questionnaire is a high-quality tool used to evaluate neuropathic and nonneuropathic pain conditions [29]. It provides basic information for pain research. The questionnaire will be administered at baseline, the 1st, 2nd, 3rd and 4th weeks of the treatment period, and at the 1-, 2-, 3- and 6-month follow-ups after treatment.

### rs-fMRI data acquisition

The rs-fMRI scan will be collected with a 3.0 Tesla superconductor (Skyra, Siemens, Erlangen, Germany) in Guang’anmen Hospital. Participants will undergo rs-fMRI scans at baseline and after the 4th week of treatment. Before the scan, participants will be asked to wear earplugs and remove all metal objects from their bodies. Relevant regulations and procedures of the MRI room will be strictly observed. Using foam pads to reduce head movement, participants will be required to remain supine and awake during the entire scan.

Whole cerebral function imaging adopts a T2-weighted echo planar imaging (EPI) sequence for axial scanning, taking the mid-sagittal parallel connection (AC-PC) as the positioning line. Scanning parameters are as follows: number of layers 47, repetition time (TR) = 3000 ms, echo time = 30 ms, layer thickness = 3.0 mm, field of view (FOV) =220 mm × 220 mm, flip angle = 85°, size of voxel = 3.0 mm × 3.0 mm, in-plane resolution = 64 × 64, phase resolution = 100%, and data collection time = 12:30s.

### DTI scanning

Axial scanning will be performed using a single excitation echo plane imaging (SE-EPI) sequence, taking the mid-sagittal parallel connection (AC-PC) as the positioning line. Scanning parameters are as follows: number of layers 60; repetition time (TR) = 11000 ms; echo time = 98 ms; layer thickness = 2.0 mm; field of view (FOV) = 256 mm × 256 mm; flip angle = 90°; size of voxel = 2.0 mm × 2.0 mm; take 30 directions for the diffusion sensitivity gradient, repeat the measurement twice; diffusion sensitivity coefficient *b* value 1000s/mm^2^; axial scanning obtains no gradient diffusion weighted imaging (*b* = 0); and data collection time = 12:52 s.

### MRS scanning

Hydrogen proton magnetic resonance spectroscopy and 3D multivoxel spectroscopy scanning will be used. Scanning parameters are as follows: repetition time (TR) = 1750 ms, echo time = 144 ms, layer thickness = 5.0 mm, repeat time = 128, and data collection time = 4:24 s.

### Treatment of adverse events (AEs)

While focusing on efficacy, researchers must be alert to the occurrence of adverse reactions or AEs. When an AE is discovered, researchers will take necessary measures to treat the condition until the adverse event resolves. Adverse reactions or AEs, whether related to the study or not, will be recorded in detail, including date of onset, signs and symptoms, examination index, outcome, date of resolution, any actions taken, duration and follow-up. AEs should be resolved within 24 h. The common treatment-related AEs include fainting due to needle stick, subcutaneous haemorrhage, redness and swelling of the acupuncture site and continuous pain at acupuncture site.

### Quality control and assurance

Before this study begins, all researchers will conduct a unified, standardized operation training to ensure that they are proficient in the treatment protocols and evaluation techniques; this training will improve the reliability of the study results. In this study, first, the laboratory examination index and normal value range will be defined, and standard operating procedures (SOPs) will be formulated to strictly control the quality of the laboratory examination index. In the process of rs-fMRI scanning, the magnetic resonance inspection requirements will be strictly followed and will include quality control of the subjects’ scanning state, the scanning equipment, the magnetic field and the image acquisition to ensure the quality and reliability of the study data. During the treatment period, scientific standards of informed consent, active health education, strengthened humane care, long-term follow-up plans and other means to improve subject compliance will be implemented.

According to the relevant requirements of the State Administration of Traditional Chinese Medicine and the study group, clinical research SOPs will be formulated to ensure that established procedures are followed throughout clinical research. The Data Monitoring Committee is composed of members of the Ethics Committee, and the committee has determined that there is no conflict of interest with this experiment. A data acquisition and management system has been set up and includes double entry for two persons, data entry personnel and researchers, to complete the first and second entry, respectively, with a third person checking to ensure the objectivity, authenticity and accuracy of the study data. Quality control of the data will be handled at least once every 4 months.

After blind auditing of the data, we believe that the established database will be correct, and the data will be locked by the main researchers and statisticians. The locked data file will not be allowed to change again. The database will be submitted to statisticians for statistical analysis according to the requirements of the statistical plan.

### Sample size calculation

This proposed study is an RCT whose primary aim is to evaluate the cerebral imaging mechanism of acupuncture to improve cerebral central sensitization and the clinical effect of acupuncture in patients with PDPN. Acupuncture is a complex intervention that differs from other treatments. Its therapeutic effect is changed if the acupoints are altered. No two-arm, randomized, sham-controlled trial has been conducted on this topic. For this reason, we are using our previous clinical experience to calculate the efficacy of electroacupuncture as an intervention [30, 31]. The proposed sample size of this trial was calculated mainly based on the Short-Form McGill Pain Questionnaire and the assumption that after treatment, the average change reported using this questionnaire would be greater for the experimental group than for the control group. The mean difference was 0.81, with a standard deviation of 0.07. Sample size was calculated using a noninferiority comparison. We set the alpha risk (*α*, type 1 error risk) at 0.025, the beta risk (*β*, type 2 error risk) at 0.2 and the critical value (*Δ*) at − 0.1. Calculating by using SAS [32], the sample size result was 24. Thus, according to this sample size calculation, each group should recruit 24 participants. Allowing for a 20% attrition rate in this study, we plan to recruit 150 participants, with 30 in each of the study groups. Healthy participants will not receive any treatment. Each participant will receive 2 rs-fMRI scans to observe different cerebral activities before and after acupuncture treatment.

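### The printed sample-size inputs do not give 24 per group: they give the minimum of 2, or 8 to 9 on the most generous reading, and the article does not show which figure is misreported

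*Protocol article*

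**What the plan says.** The Sample size calculation section names its endpoint: "The proposed sample size of this trial was calculated mainly based on the Short-Form McGill Pain Questionnaire". It assumes that the average change on this questionnaire will be greater in the experimental group than in the control group. The numerical inputs follow:

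- Effect and spread: "The mean difference was 0.81, with a standard deviation of 0.07".
- Type of test: non-inferiority.
- Error rates: 0.025 for type 1 and 0.2 for type 2, so 80% power.
- Margin, printed as "the critical value (*Δ*) at − 0.1".

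The output of the SAS run is reported in these words: "the sample size result was 24. Thus, according to this sample size calculation, each group should recruit 24 participants". A 20% attrition allowance then leads to 30 per group and 150 in total. The section does not say whether alpha is one-sided or two-sided. The article gives no other SD, variance or effect size. For the inputs it points only to the group's previous clinical experience, with two citations.

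**The concern.** A difference of 0.81 with an SD of 0.07 is a standardised effect of 0.81/0.07 = 11.6. Measured from the margin, the distance is 0.91, or 13 SDs. No trial needs 24 per group to detect an effect of that size, so the stated result cannot follow from the stated inputs.

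This is the only power statement in the article, and the recruitment target of 30 per group and 150 in total rests on it. If inputs and result do not connect, a reader cannot tell what difference between electroacupuncture and sham the trial can detect. The framing adds to the difficulty: the section assumes a larger change with the experimental treatment, which is a superiority premise, but sizes a non-inferiority test.

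**Working it through.** **Inputs, all from the Sample size calculation section.** Mean difference 0.81; SD 0.07; margin −0.1; alpha 0.025; beta 0.2; stated result 24 per group. Allocation is 1:1 within each diabetes stratum (Random allocation section). Assumption: alpha is one-sided, as is usual for non-inferiority.

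**Formula.** n per group = 2(z₀.₉₇₅ + z₀.₈₀)² × SD² / D², where D is the distance between the assumed true difference and the null value. The constant is 2(1.960 + 0.842)² = 15.698.

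**Step 1. Reproduce the plan's figure from its own inputs.** D = 0.81 + 0.1 = 0.91.
n = 15.698 × 0.0049 / 0.8281 = 0.09 per group.
A two-sample t test needs at least 2 per group, and at 2 per group its power is already 99.97%. At 24 per group power is about 100%, not 80%. The figure of 24 is not reproduced.

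**Step 2. Other standard readings with SD 0.07.**

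| Reading | D | n per group (normal formula) | Whole number: normal / t test |
|---|---|---|---|
| Non-inferiority, true difference 0.81 | 0.91 | 0.09 | 1 / 2 |
| Superiority, no margin | 0.81 | 0.12 | 1 / 2 |
| Superiority by a margin of 0.1 | 0.71 | 0.15 | 1 / 2 |
| Non-inferiority, true difference 0 | 0.10 | 7.69 | 8 / 9 |

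The last row is the most favourable to the stated figure, and it leaves the printed 0.81 unused. Trying one-sided alpha of 0.0125 or 0.05 at 80% power gives at most 11 per group. With SD 0.07, a requirement of 24 per group corresponds to D = 0.07 × 2.802 / √12 = 0.057, which matches nothing in the section.

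**Step 3. What would give 24?** Each route below changes at least one printed input.

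- SD about 1.0, no margin: 15.698 × 1 / 0.6561 = 23.9, so 24 per group by the normal approximation. An exact t test needs 25; its power at 24 per group is 78.4%.
- SD about 1.125, margin kept: 15.698 × 1.2656 / 0.8281 = 24.0 per group.
- SD 0.7, no margin: 15.698 × 0.49 / 0.6561 = 11.7, so 12 per group and 24 in total.

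**Step 4. The attrition step.** 24 / (1 − 0.20) = 30, and 5 × 30 = 150. This step is consistent, so the break lies between the inputs and 24.

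**Step 5. What the planned size detects, without needing an SD.** For a two-sided 0.05 t test at 80% power, the detectable difference is 0.83 SD with 24 completers per arm and 0.74 SD with 30.

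**The case against.** The strongest reply is that this is a reporting slip with limited reach. The abstract makes imaging the primary outcome and pain scales secondary, the trial was already recruiting, and the attrition arithmetic is sound. It can also be said that the result of 2 per group depends on one reading. Sidedness is not stated, and a non-inferiority test planned at a true difference of zero gives a larger number.

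The point about readings stands but does not rescue the figure, because the most generous reading at alpha 0.025 still gives only 8 or 9. The point about reach limits the consequence to the reporting of one paragraph. That paragraph is still the article's only justification of its size.

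Three stronger inferences are tempting, and the document supports none of them.

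- **That the SD is the misprint.** It would be if the difference and margin were known to be right. The article does not establish that, and either could be misreported instead.
- **That 0.81 must be a standardised effect.** This reproduces 24 neatly by the normal approximation, but so does an SD of 1.125 with the margin, and an SD of 0.7 gives 24 as a total. All are guesses about SAS inputs that are not shown.
- **That the trial is underpowered.** Power for a difference of 0.81 depends on an SD that the article does not usably give. Any low figure would come from an assumed SD.

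**Conclusion.** The stated 24 per group does not follow from the stated inputs. They give 0.09 per group (2 in practice), or 8 to 9 if the true difference is taken as 0. The printed difference, SD, margin and n cannot all be right, and the article does not identify the wrong one. Because one reconstruction gives 12 per group, 24 may even be a total misread as a per-group number.

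The step 1 and step 2 results rest on 1:1 allocation, a two-sample comparison of means and one-sided alpha 0.025; the other alphas tried do not change the conclusion. Nothing here shows that 30 per arm is too few or too many. It shows that the stated 80% power cannot be traced, which should be corrected because no other power statement exists.

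**What to change.** Rewrite the sample-size paragraph to:

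- report the inputs actually entered in SAS, with the source of the mean difference and the SD;
- state whether alpha is one-sided or two-sided, and whether 24 is per group or total;
- reconcile the non-inferiority calculation with the stated assumption that the change is greater with electroacupuncture than with control;
- keep the planned 30 per arm and restate the power it delivers, before and after the 20% attrition;
- if no usable SD of the questionnaire change exists, give instead the detectable electroacupuncture-versus-sham difference at 80% power and two-sided 0.05: 0.83 SD with 24 completers per arm, 0.74 SD with 30;
- say that the calculation covers the electroacupuncture-versus-sham contrast in participants with PDPN. The size of the other groups, including the untreated healthy group, is then a design choice and not a result of this calculation.

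The cost is one paragraph and no added participants. The downside is that the stated power may become less favourable once the true inputs are shown.

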## Method

### Study setting/design

This two-armed randomized, sham-controlled clinical trial will be performed at Guang’anmen Hospital (China Academy of Chinese Medical Sciences) and the Affiliated Hospital of Changchun University of Traditional Chinese Medicine. The study protocol has been approved by ethics committees at both participating hospitals. The clinical trial has been approved by the Ethics Committee of the Affiliated Hospital of Changchun University of Traditional Chinese Medicine (CCZYFYLL2018-002) and by Guang’anmen Hospital (China Academy of Chinese Medical Sciences) (2019-070-KY-02), and it was registered with ChiCTR of the Chinese Clinical Trial Registry (NO: ChiCTR1900024109). A flow chart of the trial is shown in Figs. 1 and 2. This study will be reported based on the STandards for Reporting Interventions in Clinical Trials of Acupuncture (STRICTA) checklist [20] and the Standard Protocol Items: Recommendations for Interventional Trials (SPIRIT) checklist [21] (Table 1 and Additional file 1).

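### The sample size is framed as non-inferiority to an inactive sham (critical value -0.1), which fits neither the trial's question nor its planned difference tests

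*Protocol article*

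**What the plan says.** The Study setting/design section opens with "This two-armed randomized, sham-controlled clinical trial will be performed at", and two hospitals are then named. Under Sham electroacupuncture, the control is blunt needles that do not enter the skin, with the stimulator lead cut. The Discussion says the sham groups are there because of placebo effects.

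The Sample size calculation section is based mainly on the Short-Form McGill Pain Questionnaire. Its expectation is that "the average change reported using this questionnaire would be greater for the experimental group than for the control group". For the numbers, it takes a difference in means of 0.81 and an SD of 0.07. The framework is given in one sentence: "Sample size was calculated using a noninferiority comparison". Type 1 error is 0.025 and type 2 error is 0.2, with no word on sidedness. The margin appears as "the critical value (*Δ*) at − 0.1", without a reason for its size. The result is 24 per group, raised to 30 for 20% attrition.

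The Clinical data analysis section lists a t test, a rank sum test and analysis of variance, and states: "Changes between groups before and after treatment will be analysed by ANOVA". It mentions no margin.

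**The concern.** Non-inferiority asks whether a treatment is not unacceptably worse than a comparator. That is informative when the comparator is known to work. Here the comparator is built to be inactive, and the question is whether electroacupuncture does more than sham. With a larger change favourable and a critical value of -0.1, the sizing null is that electroacupuncture is worse than sham by 0.1 or more. A true effect of zero, or anything down to just above -0.1, lies in the alternative. Rejecting that null cannot show that electroacupuncture beats sham.

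The sizing hypothesis therefore disagrees with three other statements in the article: the expectation of a greater change in the same paragraph, the reason given for the sham arms, and the difference tests in the analysis section. The article justifies neither the framework nor the value 0.1. At stake is what the stated sample size and power refer to, and whether a later report could point to the protocol in support of a claim of non-inferiority to sham, which would say nothing about efficacy.

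**Working it through.** **Inputs (Sample size calculation section).** Mean difference 0.81, SD 0.07, critical value -0.1, alpha 0.025 (sidedness not stated; taken as one-sided, as is usual for non-inferiority), power 0.80, 24 per group. Allocation is 1:1 (Random allocation section).

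**1. The plan's own figure.** By normal approximation, n per arm = 2 × [SD × (1.960 + 0.842) / (true difference + margin)]².

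- True difference 0.81, margin 0.1, SD 0.07: 2 × (0.07 × 2.802 / 0.91)² = 0.09, so 1 per arm (2 by exact t).
- True difference 0, margin 0.1, SD 0.07: 2 × (0.07 × 2.802 / 0.1)² = 7.7, so 8 per arm (9 by exact t).

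Neither gives 24. Solving for the SD that does, SD = effect / (2.802 × √(2/24)):

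- non-inferiority, effect 0.91: SD 1.13
- superiority, effect 0.81: SD 1.00

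The attrition step does reproduce: 24 / 0.8 = 30.

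**2. How often a treatment with no benefit would meet the margin.** With 24 per arm, the standard error is SD × √(2/24). The probability of rejecting the sizing null comes from the non-central t distribution with 46 degrees of freedom and non-centrality (true difference + 0.1) / standard error.

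| SD | True difference | Meets -0.1 | Superiority shown |
|---|---|---|---|
| 0.07 (stated) | 0 | 99.8% | 2.5% |
| 0.07 (stated) | -0.05 | 67.8% | below 0.1% |
| 1.0 (assumed) | 0 | 5.3% | 2.5% |
| 1.0 (assumed) | -0.05 | 3.7% | 1.7% |

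For the first row, the standard error is 0.07 × 0.2887 = 0.0202 and the non-centrality is 0.1 / 0.0202 = 4.95. For the third, the standard error is 0.2887 and the non-centrality is 0.35. The normal approximation gives 99.9%, 69.7%, 5.3% and 3.7% in the margin column.

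**3. What a superiority framing implies for 24 per arm.** One-sided 0.025, 80% power, difference 0.81, normal approximation:

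- SD 0.07: 1 per arm (2 by exact t), so the stated SD gives no usable size.
- Assumed SD 0.7: 12 per arm.
- Assumed SD 1.0: 2 × (2.802 / 0.81)² = 23.9, so 24 per arm.
- Assumed SD 1.125: 31 per arm.

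At SD 1.0, non-central t gives 78.4% power with 24 per arm and needs 25 for 80%. Recruiting 30 leaves 30 × 0.8 = 24; leaving 25 would need 25 / 0.8 = 31.25, so 32. Under the stated non-inferiority design, SD 1.0 would need only 20 per arm by exact t.

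**The case against.** The strongest reply is that non-inferiority appears only in the sample size paragraph. A reader might infer that a zero effect would be called a success, or that the trial could not tell whether electroacupuncture works. The article supports neither. It makes no rule out of meeting -0.1, and the planned t tests and analyses of variance address a difference from sham, with a null effect declared at the usual error rate. The lack of a written decision rule is not a fault either, because the article refers to a separate statistical plan that is not shown. This part of the objection stands, and it limits the point to a wrong sizing hypothesis that conflicts with the planned tests.

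The reply also has force on size. A reader might take 99.8% as the trial's error rate. It needs the SD of 0.07, and with that SD the stated inputs give 1 or 2 per arm, so 0.07 is unlikely to be what produced 24. At an SD near 1 the excess is modest.

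A reader might equally infer that 24 is exactly the superiority number and nothing else need change. That holds only if 0.81 is a standardised difference and the normal approximation is used. The article presents 0.81 as a mean difference beside an SD of 0.07.

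What the reply does not answer is why a trial against an inactive sham, expecting a greater change, was sized by non-inferiority at all.

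**Conclusion.** The point holds as a defect in the stated sizing hypothesis. It contradicts the expectation in its own paragraph, the purpose of the sham arms and the difference tests planned later, and it needs correcting. It is not a finding that the trial will declare success on a null effect.

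Its numerical weight cannot be fixed from the article, because the SD is in doubt: the chance that a zero effect meets the margin runs from 5.3% at an assumed SD of 1 to 99.8% at the stated 0.07, against 2.5% under superiority. These figures assume 24 evaluable participants per arm, one-sided alpha 0.025, and larger change as the favourable direction. That a null effect satisfies the sizing alternative does not depend on the SD.

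**What to change.** In the Sample size calculation section, replace the non-inferiority sentence with superiority of electroacupuncture over sham on change in Short-Form McGill score in PDPN participants, at two-sided alpha 0.05 (the same as one-sided 0.025), and delete the critical value of -0.1. Base any efficacy conclusion on that measure on the 95% confidence interval for the difference excluding zero in favour of electroacupuncture, in line with the difference tests in the Clinical data analysis section. This wording covers only the measure used for sizing. It does not settle which outcome is primary: the abstract names imaging, and the McGill scale appears under both primary and secondary outcomes.

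Verify the SD against its source and restate the justification. If 0.81 proves to be a standardised difference, report that 24 evaluable per arm gives about 78% power by non-central t (80% by normal approximation), rather than presenting 24 as exact. If the SD on the score scale is something else, recompute; the assumed range 0.7 to 1.125 gives 12 to 31 per arm.

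The cost is a change of wording, one recalculation and possibly a slightly lower stated power. Whether the sample size itself must change depends on the verified SD.
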